### Statistical analysis plan

Analyses of both the intention-to-treat and per-protocol populations will be presented. Statistical analyses will be descriptive in nature (counts/proportions, or GMT where appropriate). Any comparative statistics (χ^2^/Fisher’s-exact or paired/unpaired t-test where appropriate) and analyses of exploratory/longitudinal data will be post-hoc analyses.

The full details of the analysis will be provided in the statistical analysis plan which will be finalised prior to unblinding and database lock.

Interview transcripts will be analysed qualitatively.

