**Methods and analysis:**

This is a single-centre, randomised, single-blinded, vaccine safety and immunogenicity study in healthy adults living in Rwanda. Seventy-two participants will be randomised in a 1:1 ratio to two study groups, the first receiving rVSVΔG-ZEBOV-GP with a placebo, the second group receiving rVSVΔG-ZEBOV-GP concurrently with a Pfizer–BioNTech COVID-19 booster dose. The primary outcome measures are quantitative serum anti-glycoprotein (GP) antibody responses, as measured by ELISA, 28 days after vaccination, and frequency and severity of adverse events in the 7 days following vaccination. Secondary outcome measures include day 28 and day 180 serum anti-GP and serum SARS-CoV-2 anti-spike protein-specific geometric mean antibody titres.

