### Trial design and setting

This is a single-centre, randomised, participant-blinded, vaccine safety and immunogenicity study in healthy adults living in Rwanda. The EbolaCov trial aims to inform whether the Ebola vaccine rVSVΔG-ZEBOV-GP can be administered concurrent to a Pfizer–BioNTech COVID-19 booster dose without an unacceptable increase in reactogenicity and/or loss of humoral immunogenicity to Ebola vaccine antigen.

This trial is being conducted at the research and healthcare facility the Center for Family Health Research in Kigali, Rwanda, in collaboration with Rwanda Biomedical Centre, the national central health implementation agency for Rwanda.

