### Objectives and outcomes

The primary safety objective is to determine the frequency and severity of severe solicited systemic adverse reactions within 1 week of concurrent vaccine dose administration, compared with giving the rVSVΔG-ZEBOV-GP vaccine alone. Participant-reported reactogenicity data will be entered via an e-diary or a backup paper diary. Data includes solicited adverse events (AEs), including injection site reactions (pain, tenderness, erythema, swelling, axillary swelling or tenderness), as well as systemic symptoms (headache, malaise, myalgia, nausea, vomiting and fever). AEs of special interest include arthritis, synovitis, joint effusions, temporomandibular joint syndrome, tendonitis, mucosal or skin lesions and postvaccination dermatitis. All AEs will be graded in severity by the participant and then reviewed by the study team. Relationship to the trial vaccines will be determined by a study physician.

The primary immunogenicity objective is to measure serum anti-GP antibody responses 28 days after concurrent vaccine dose administration, compared with giving the rVSVΔG-ZEBOV-GP vaccine alone. This outcome will be measured using day 28 serum anti-GP antibody responses assessed by commercially available ELISA.

Secondary objectives include longitudinal assessment of humoral response to rVSVΔG-ZEBOV-GP and SARS-CoV-2 when co-administered with Pfizer–BioNTech COVID-19 booster vaccination, compared with giving the rVSVΔG-ZEBOV-GP vaccine alone, and assessment of SARS-CoV-2 anti-spike protein specific geometric mean titres (GMT) when co-administered with rVSVΔG-ZEBOV-GP vaccine. Secondary immunogenicity outcome measures include day 28 and day 180 anti-GP and anti-spike GMT measured by commercially available ELISA.

We also aim to evaluate the perceptions and acceptability of concurrent vaccination among healthcare workers and volunteers who took part in the study using transcripts from semi-structured interviews (or focus groups) conducted for this purpose.

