### Sample size

No studies have analysed the concurrent administration of rVSV-vector and lipid-enveloped mRNA vaccine technologies to provide a basis for power calculations.

Published data from clinical trials of rVSVΔG-ZEBOV-GP showed an anti-GP serum antibody GMT of 994.7 (915–1081, SD 38.9)^5 7^ 28 days after vaccination. These data help to design a study to investigate humoral immune responses to vaccination in the context of concurrent dosing with an mRNA COVID-19 product. A standard significance (alpha) value of 5% and 80% power were applied for a statistically significant likelihood of detecting any inferior GMT responses to rVSV-ZEBOV-GP between study groups. A 25% non-inferiority margin was selected, in line with the previous co-administration studies.^12^ Pragmatically, it enables a deliverable, while clinically meaningful, phase IV co-administration study that is the first examination of rVSV-ZEBOV-GP and mRNA vaccine technology as co-administration where Ebola immune correlates of protection are unknown. A 10% non-inferiority margin would require large cohort sizes that exceed operational capacity (with this margin the requirement would be n=188 per group). A cohort size of 32 was calculated in line with these parameters.^18^ An additional 10% recruitment margin is added as contingency for participant withdrawal or dropout before day 28. This finalises each cohort size at 36 participants, totalling 72 participants.

The study population size is not powered for comparative serum anti-spike protein antibody responses due to impractical cohort sizes and wider variation in GMT distribution and CIs: a statistically significant non-inferior response 28 days after third dose boosting (Pfizer–BioNTech; GMT 1789, 1520–2107, SD 134.5) would require a cohort size of n=359.^16^ The sample sizes reflect operational delivery expectations and also afford stability of estimates in reactogenicity and immunogenicity data not formally powered for.

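### The safety half of the aim is comparative, but the article plans only counts plus post-hoc χ²/Fisher tests, and neither can bound an excess of severe reactions at 36 per group

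*Protocol article*

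**What the plan says.** All references are to the Protocol article.

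- **Aim** (Trial design and setting; also the Abstract). The trial is to inform whether the Ebola vaccine can be given with the COVID-19 booster "without an unacceptable increase in reactogenicity and/or loss of humoral immunogenicity to Ebola vaccine antigen".
- **Primary outcomes** (Abstract, Methods and analysis). One is the day-28 anti-GP antibody response. The other is "frequency and severity of adverse events in the 7 days following vaccination".
- **Primary safety objective** (Objectives and outcomes). The article words it as follows: "determine the frequency and severity of severe solicited systemic adverse reactions within 1 week of concurrent vaccine dose administration, compared with giving the rVSVΔG-ZEBOV-GP vaccine" (meaning the Ebola vaccine without the booster). It is therefore worded as a comparison between groups.
- **Analysis** (Statistical analysis plan). "Statistical analyses will be descriptive in nature (counts/proportions, or GMT where appropriate"), and then "Any comparative statistics (χ^2^/Fisher’s-exact or paired/unpaired t-test where appropriate) and analyses of exploratory/longitudinal data will be post-hoc analyses". The section adds: "The full details of the analysis will be provided in the statistical analysis plan which will be finalised prior to unblinding and database lock".
- **Sample size.** The 25% margin and 80% power concern the antibody response only. The size is also said to "also afford stability of estimates in reactogenicity and immunogenicity data not formally powered for". The strengths and limitations box likewise says that power exists only for the antibody response at one month.

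**The concern.** A conclusion that co-administration brings no unacceptable increase is a statement about how large an excess can be ruled out. It needs an estimate of the excess and an upper limit on it. The antibody half of the aim has a stated margin. The safety half has a comparative primary objective, but the analysis section offers only side-by-side proportions, with any test done post hoc. The tests it names have no difference as their null hypothesis.

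This is a stated choice and not just silence, because the section classes comparative statistics as post hoc. An SAP that prespecified a safety comparison would have to depart from that sentence.

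At stake is how the safety result is worded. The Safety section says there are no data on concurrent use of these two platforms, so this trial's statement may carry weight. If similar counts or a non-significant test were taken as reassurance, a small sample would make that reassurance easier to reach.

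**Working it through.** **Inputs from the article.** Allocation is 1:1. The calculated size is 32 per group with a 10% allowance: 32 / (1 − 0.10) = 35.6, rounded up to 36, which reproduces the stated figure. The article gives no power, margin or event rate for the safety outcome, so there is no safety figure to reproduce.

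**Assumptions.** Control-group rates of severe reactions of 2%, 5%, 10% and 15%; a two-sided 5% level; all 36 per group evaluable at day 7.

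**Step 1: what a test would miss.** With X1 ~ Bin(36, p) and X2 ~ Bin(36, 3p), power is the sum of P(X1 = a)·P(X2 = b) over all pairs (a, b) with b > a and test p ≤ 0.05. The miss rate is 1 − power.

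| Control → co-administration | Uncorrected χ² misses | Fisher misses |
|---|---|---|
| 2% → 6% | 91% | 99% |
| 5% → 15% | 68% | 85% |
| 10% → 30% | 42% | 53% |
| 15% → 45% | 18% | 26% |

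With 32 evaluable per group, the 5% → 15% row becomes 72% and 89%.

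Fisher's test needs at least 6/36 against 0/36, or 9/36 against 2/36, to reach p ≤ 0.05.

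**Step 2: what the data could exclude.** Let p1 and p2 be the observed proportions in groups 1 and 2, l1 the Wilson lower limit for p1, and u2 the Wilson upper limit for p2. The Newcombe 95% upper limit for p2 − p1 is

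(p2 − p1) + √[(u2 − p2)² + (p1 − l1)²].

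- 0/36 in both groups: u2 = 1.96² / (36 + 1.96²) = 3.84 / 39.84 = 0.096. The upper limit is **+9.6 points**.
- 2/36 in both groups: p = 0.0556, Wilson limits 0.0154 and 0.1814. The upper limit is √(0.1259² + 0.0402²) = 0.132, or **+13 points**.
- 5/36 in group 2 against 0/36 in group 1: p2 = 0.139, u2 = 0.287. The upper limit is 0.139 + (0.287 − 0.139) = 0.287, or **+29 points**. Fisher's p is 0.054, so this result would be reported as not significant. The uncorrected χ² gives p = 0.020 on the same table, so a post-hoc choice between the two named tests could decide the reading.

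**Step 3: expected precision when nothing is wrong.** Averaging the Newcombe upper limit over all outcomes with equal true rates at 36 per group:

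| True rate in both groups | Mean 95% upper limit for the excess |
|---|---|
| 2% | +11 points |
| 5% | +13 points |
| 10% | +15 points |
| 20% | +18 points |

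**The case against.** The strongest reply has four parts.

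**The limits are disclosed.** The article says that power exists for the antibody response only, and the stability remark itself ends by conceding that these data are not formally powered. This stands: there is no hidden power claim, and lack of power is not the point. The disclosure does not say what a comparative primary objective may conclude from unpowered data.

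**The test is not the planned basis for the safety conclusion.** A reader might infer that the trial will declare reactogenicity acceptable if p > 0.05. The documents do not say so. The analysis is descriptive and any test is post hoc. What remains is that neither route yields a bound on the excess.

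**The detail belongs in the SAP.** The article defers full details to an SAP that is not shown, so the absence of a confidence interval method is not in itself an error. This stands for the finer detail. It does not cover the published statement that comparative statistics will be post hoc, which sits badly with a comparative primary objective. The SAP need only be final before unblinding and database lock. Table 1 puts unblinding at day 180, and only participants are stated to be blinded. Nothing in the article requires the safety comparison to be fixed before the day-7 results are known.

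**A formal safety margin is a matter of preference.** Largely true. A descriptive safety outcome without a margin is a legitimate design. An interval would serve the aim without one, and a margin is needed only if the investigators want to claim that the increase is not unacceptable. The data safety monitoring committee's access to unblinded safety data protects participants but does not define that term for the final report.

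**Conclusion.** The point holds as a mismatch between a comparative primary safety objective and an analysis that cannot bound the difference. Equal observed counts would still leave an excess of about 10 points (no events) or 13 points (two events per group) within the 95% interval. With equal true rates of 2–20%, the mean upper limit is about +11 to +18 points.

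A reader might take away one headline figure, for example that a tripling would be missed 70–85% of the time. The documents do not support that, because they give no severe-reaction rate. That range fits only a control rate near 5%. From 2% the miss rate is 91–99%, from 10% it is 42–53%, and from 15% it is 18–26%, so at the highest assumed rate the test would usually detect a tripling.

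The results assume a two-sided 5% level, 36 evaluable per group and the rates listed. The unseen SAP may already supply an interval. If so, the article's sentence on post-hoc comparisons should be brought into line with it.

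**What to change.** 1. **Statistical analysis plan section.** Name the primary safety comparison: the risk difference (group 2 minus group 1) in participants with at least one severe solicited systemic reaction by day 7, with a two-sided 95% score-based interval (Newcombe or Miettinen–Nurminen). Fix it before any by-arm data are seen. It takes the place of a post-hoc χ² or Fisher test for this outcome.
2. **Interpretation.** State that neither similar counts nor a non-significant test will be described as acceptable reactogenicity, and that the report will give the largest excess the interval does not exclude. If the investigators wish to claim no unacceptable increase, they should name the acceptable excess beforehand.
3. **Sample size section.** Replace the remark on stability of reactogenicity estimates with the expected precision and its assumptions: at 36 per group with equal true rates between 0% and 20%, the 95% upper limit for the excess averages about +10 to +18 percentage points.

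The cost is a few sentences in the SAP and protocol, with no extra participants, visits or data. The drawback is that the stated safety precision looks less favourable and the safety conclusion may have to be reported as inconclusive.

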**Trial registration number:**

Pan African Clinical Trials Registry (PACTR202407764378004) and ClinicalTrials.gov (NCT06587503)

STRENGTHS AND LIMITATIONS OF THIS STUDYSafety and immunogenicity data following vaccine co-administration will be invaluable knowledge for future outbreaks when conducted in the target population and populations more representative of the settings in which they are needed.The study is statistically powered for non-inferior antibody responses to rVSVΔG-ZEBOV-GP 1 month after vaccination only.This is a single-centre study, which may limit the generalisability of the results.

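### The trial is sized for non-inferiority of the day 28 anti-GP response, but the analysis section makes all analyses descriptive and any comparison post hoc, so this document prespecifies no non-inferiority test

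*Protocol article*

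**What the plan says.** Three places in the protocol article set up a non-inferiority trial.

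- Strengths and limitations: "The study is statistically powered for non-inferior antibody responses to rVSVΔG-ZEBOV-GP 1 month after vaccination only".
- Objectives and outcomes: the primary immunogenicity objective is a comparison of day 28 anti-GP responses between concurrent dosing and the Ebola vaccine alone.
- Sample size: "A standard significance (alpha) value of 5% and 80% power were applied", and "A 25% non-inferiority margin was selected, in line with the previous co-administration studies". From these the section derives 32 per group, raised to 36 for dropout (72 in total).

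The section headed Statistical analysis plan takes a different line. It says "Statistical analyses will be descriptive in nature (counts/proportions, or GMT where appropriate"), with no exception for the primary outcome. It then names χ²/Fisher's exact tests and t-tests as the possible comparative statistics and gives them this status: "or paired/unpaired t-test where appropriate) and analyses of exploratory/longitudinal data will be post-hoc analyses". Both the intention-to-treat and per-protocol populations are to be presented. Full details are deferred to an SAP, to be finalised before unblinding and database lock. The 25% margin does not appear in the analysis section.

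**The concern.** A hypothesis that fixes the number of participants should have a prespecified test. Here the sizing and the analysis sections lay down rules that cannot both be followed. If the analysis section governs, the margin plays no part in the analysis and the between-group comparison of the primary immunogenicity outcome is post hoc, which cannot carry a confirmatory claim.

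The only comparison named that suits titres is the t-test. Used in its ordinary form, as a test of no difference, it does not address whether the loss is smaller than 25%: a non-significant p-value is not evidence of non-inferiority. The trial is meant to inform whether concurrent dosing avoids a loss of humoral response, so false reassurance on this point would go to its main purpose.

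**Working it through.** **1. Which test drives the sample size?**

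Inputs, all from the Sample size section: "anti-GP serum antibody GMT of 994.7 (915–1081, SD 38.9"), margins of 25% and 10%, 80% power, alpha 5% (sidedness not stated), and anti-spike SD 134.5. The two-sample non-inferiority formula with a true difference of zero is

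n per group = 2 × [SD × (z₁₋α + z₀.₈₀) / margin]²

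The margins are entered as 25 and 10 on the same scale as the SD. With z₀.₈₀ = 0.842, z₀.₉₅ = 1.645 and z₀.₉₇₅ = 1.960, and each n rounded up:

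| Case | Stated n | One-sided 5%: normal / t | One-sided 2.5%: normal |
|---|---|---|---|
| SD 38.9, margin 25 | 32 | 30 / 31 | 39 |
| SD 38.9, margin 10 | 188 | 188 / 188 | 238 |
| SD 134.5, margin 25 | 359 | 358 / 359 | 455 |

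For example, 2 × [38.9 × (1.645 + 0.842) / 10]² ≈ 187.1, rounded up to 188, which agrees with "with this margin the requirement would be n=188 per group". For dropout, 32 × 1.1 = 35.2 and 32 / 0.9 = 35.6, and both round up to 36.

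The stated sizes are therefore close to a one-sided 5% non-inferiority calculation and do not fit one-sided 2.5%. The one-sided level is inferred from this match.

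**2. What does an ordinary t-test of difference do at the margin?**

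Read the 25% margin as a GMT ratio of 0.75. Take n = 32 per group (df = 62), a two-sided 5% t-test on log titres, and a true ratio of exactly 0.75. The document gives no log-scale SD, so log10 SD from 0.2 to 0.5 is assumed.

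- SD on the natural log scale: s = log10 SD × 2.303
- Standard error: SE = s × √(2/32) = s / 4
- Noncentrality: δ = |ln 0.75| / SE = 0.2877 / SE
- P(non-significant) = P(|T| < 1.999), with T noncentral t (df 62, noncentrality δ)

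**3. What power does a ratio-scale non-inferiority test have?**

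For a true ratio of 1 and margin 0.75, δ is the same. Power is P(T > 1.670) at one-sided 5% (90% CI) and P(T > 1.999) at one-sided 2.5% (95% CI).

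| log10 SD (assumed) | SE | δ | t-test non-significant at true ratio 0.75 | NI power, one-sided 5% | NI power, one-sided 2.5% |
|---|---|---|---|---|---|
| 0.2 | 0.115 | 2.50 | 31% | 80% | 69% |
| 0.3 | 0.173 | 1.67 | 63% | 50% | 37% |
| 0.4 | 0.230 | 1.25 | 77% | 34% | 23% |
| 0.5 | 0.288 | 1.00 | 83% | 26% | 16% |

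At a true ratio of 0.75, a one-sided 5% non-inferiority test wrongly passes in at most 5% of trials, whatever the SD.

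**4. Does the planned power carry over?**

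No. The plan's inputs are a difference of 25 with SD 38.9. If those are titre units, 25 / 994.7 is about 2.5% of the reference GMT, not 25%. Whatever scale was meant, the calculation is not one for a ratio of 0.75 on log titres, so its 80% says nothing about the power of that test.

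**The case against.** The strongest reply is that the analysis section defers full details to an SAP fixed before unblinding. The estimator, the confidence-interval criterion and the primary population are things an article may properly leave there. That stands, and their absence is not the point. A reader might infer that non-inferiority will never be tested; the document does not support this, because the SAP could still add the test. What deferral does not remove is the pair of positive statements, descriptive and post hoc, which an SAP must either follow or contradict.

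One could also read the post-hoc label as covering exploratory and longitudinal data only. The sentence joins comparative statistics and exploratory analyses with *and*, so both take the label, and the preceding sentence makes the analyses descriptive without exception.

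A third reply is that naming a t-test does not commit the trial to a test of equality. An unpaired t procedure on log titres also yields the confidence interval needed, and nothing says that a non-significant result will be read as no loss. This is fair. The 31% to 83% figures show what would follow from that misreading; they do not describe a stated plan. Nor can one say that the misreading would usually reassure wrongly: at log10 SD 0.2 it does so in under a third of trials.

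The Sample size section also says "A standard significance (alpha) value of 5% and 80% power were applied for a statistically significant likelihood of detecting any inferior GMT responses". Taken alone, this describes the reverse of showing non-inferiority. The sentence after it names a non-inferiority margin, so this is loose wording and not a separate error.

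Finally, a reader might conclude that the trial has 72% power, not 80%, if a 95% CI is used. That figure comes from SD 38.9 and a difference of 25 with 32 per group. It is not the power of a ratio-scale test and should not be quoted as such.

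**Conclusion.** The concern holds as a contradiction within the protocol article. The trial is sized for non-inferiority of the primary immunogenicity comparison, while the analysis section makes the analyses descriptive and any comparison post hoc. As it stands, this document contains no prespecified non-inferiority test, and an SAP faithful to the analysis section could not support a confirmatory conclusion.

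The contradiction rests on the text alone and needs no assumption. Its possible consequence, a non-significant t-test mistaken for non-inferiority, depends on the assumed log10 SD: about 31% of trials at 0.2, rising to 83% at 0.5, against at most 5% for the proper test. These figures take the margin as a ratio of 0.75 and 32 evaluable participants per group. It must be fixed, because a confirmatory rule cannot credibly be added once the data are unblinded.

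**What to change.** Before unblinding, amend the analysis section and carry the same text into the SAP:

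- Primary immunogenicity analysis: the day 28 anti-GP GMT ratio (Group 2 / Group 1), estimated on log titres, with its lower confidence limit compared with 0.75.
- State the sidedness of alpha and the matching interval. One-sided 5%, that is a two-sided 90% CI, is the level that the stated sample sizes approximately match.
- Report the result in both the intention-to-treat and per-protocol sets.
- Confine the descriptive and post-hoc labels to secondary and exploratory outcomes.
- Restate the power for this ratio-scale test at the chosen CI level, with a justified log-scale SD. Power of 80% with 32 per group at one-sided 5% needs a log10 SD of about 0.2.

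The cost is a few sentences in the protocol and SAP and one power calculation. Prespecifying the test needs no extra participants or visits. If the restated power proves low, that should be declared as a limit on what the trial can conclude.

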### Blood sampling

A 20 mL blood sample will be collected at enrolment, day 28 and day 180 for laboratory analyses to assess the objectives defined above and antibody responses to vaccination only, and there is no storage of cells or DNA. Laboratory analyses will be performed at the research site (Center for Family Health Research, Kigali) or at the Rwanda Biomedical Centre reference laboratory in Kigali. The GMT and antigen-specific antibody titre will be measured by commercial GP-ELISA 28 days and 180 days after vaccination.

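### Only t-tests are named for comparing titres although day 0 serum is drawn from everyone; a log-titre ANCOVA on day 0 titre should be pre-specified, as precision may otherwise be forgone

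*Protocol article*

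**What the plan says.** The Statistical analysis plan section of the Protocol article sets a descriptive frame: "Statistical analyses will be descriptive in nature (counts/proportions, or GMT where appropriate". Comparisons, if made, are labelled post hoc. They use chi-square or Fisher's exact tests for counts and, for continuous data, "paired/unpaired t-test where appropriate". No covariate-adjusted model is mentioned. The section then defers: "The full details of the analysis will be provided in the statistical analysis plan which will be finalised prior to unblinding and database lock".

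On the data available, the Blood sampling section says "A 20 mL blood sample will be collected at enrolment, day 28 and day 180", and Table 1 also lists serology at day 0. The assay sentence in the same section reads "antigen-specific antibody titre will be measured by commercial GP-ELISA 28 days and 180 days after vaccination" and does not list day 0.

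On the question, Objectives and outcomes sets a between-group comparison of anti-GP response: "This outcome will be measured using day 28 serum anti-GP antibody responses assessed by commercially available ELISA". Anti-GP and anti-spike GMTs at days 28 and 180 are secondary outcomes.

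**The concern.** The primary immunogenicity question is a contrast between two randomised groups at day 28. Of the two tests named, the unpaired t-test addresses that contrast but does not use the day 0 titre. The paired t-test uses it, but answers a within-group before-and-after question. Neither combines the two.

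This matters because precision is scarce. The Sample size section plans on 32 evaluable participants per group, recruits 36, and says that a cohort large enough for a tighter margin exceeds operational capacity. The choice of analysis is one of the few levers left. If day 0 titre predicts later titre, a chance imbalance at day 0 shifts the unadjusted GMT ratio in proportion to the baseline slope. ANCOVA on the log scale removes that shift and the variance that goes with it.

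**Working it through.** **Inputs from the article.** 32 evaluable per group, 36 recruited; 25% non-inferiority margin; alpha 5%, power 80%; reference SD 38.9 for anti-GP (all Sample size). **Inputs not in the article.** The correlation r between day 0 and later log titre, and the between-person SD of log titre. Both are assumed below and shown as ranges.

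**1. The plan's own figure.** For an unadjusted two-group comparison with one-sided 5%, n per group = 2(1.645 + 0.842)² × SD² / margin².

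- Margin 25, SD 38.9: 2 × 6.18 × 1513.2 / 625 gives 30 (31 with the t distribution), against 32 stated.
- Margin 10, SD 38.9: 188, against 188 stated.
- Anti-spike, margin 25, SD 134.5: 358 (359 with the t distribution), against 359 stated.

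So the trial was sized on an unadjusted comparison. The figures come back only if the percentages are entered as raw titre units. That is a separate matter, and baseline adjustment does not touch it.

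**2. Effect of adjusting for day 0 titre.** The variance of the adjusted log GMT ratio is about (1−r²) times the unadjusted one. Estimating the slope costs one degree of freedom, allowed for by the factor 1 + 1/(2n−4). With n = 32 this is 1 + 1/60 = 1.017.

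| r (assumed) | 1−r² | with lost df | change in variance | adjusted n per group matching 32 unadjusted, 32(1−r²) rounded up |
|---|---|---|---|---|
| 0 | 1.000 | 1.017 | +1.7% | 32 |
| 0.1 | 0.990 | 1.006 | under +1% | 32 |
| 0.2 | 0.960 | 0.976 | −2.4% | 31 |
| 0.3 | 0.910 | 0.925 | −7.5% | 30 |
| 0.5 | 0.750 | 0.762 | −24% | 24 |
| 0.7 | 0.510 | 0.518 | −48% | 17 |

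The last column leaves out the lost degree of freedom. Break-even is where (1−r²) × 61/60 = 1, so r² = 1/61 and r is about 0.13. Below that, adjustment costs at most 1.7% of variance.

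**3. What it does for power.** Take a GMT ratio margin of 0.75, one-sided 5%, 32 per group and an assumed log10 SD of 0.4. Power = Φ(0.2877 / (0.4 × 2.3026 × √((1−r²) × 2/32)) − 1.645). This gives 35% unadjusted, 37% at r = 0.3, 42% at 0.5 and 54% at 0.7. For log10 SD from 0.3 to 0.5 and r from 0 to 0.7, power runs from 26% to 75%. Adjustment helps, but nowhere in this assumed range does it restore 80%.

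**The case against.** The strongest reply is that the t-test is not fixed as the primary analysis. It sits in a general parenthesis, qualified and labelled post hoc, and full detail is left to a SAP that is not shown and could specify ANCOVA. An unadjusted comparison in a randomised trial is also valid and unbiased. All of this is correct, and it limits the point to a recommendation. It does not remove it, because the article states a method instead of staying silent, and that method has a better alternative given the samples already drawn.

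A reader might infer three stronger things that the documents do not support.

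- **That titres will be tested on the raw scale.** The section does not say so. It names GMT as the summary, and a t-test on log titres does compare GMTs as a ratio.
- **That day 0 sera will go untested.** The assay sentence gives days 28 and 180, which may simply be the outcome times. The same section says that the enrolment sample also serves the objectives. This calls for confirmation; it is not a demonstrated gap.
- **That the paired test is misplaced.** Longitudinal assessment is a secondary objective, and a paired test has a natural use there. It is only unsuited to the between-group question.

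**Conclusion.** The point holds as a modest, cheap improvement: the only continuous-data comparison named does not use day 0 titre for the between-group contrast, and precision may be forgone as a result. It would be too strong to say that precision is lost. The size depends wholly on r, which the article does not give: about nil at 0.1 or less, 2% of variance at 0.2, 7.5% at 0.3 and 24% at 0.5.

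For anti-GP the gain may be small. If most participants have uniformly low titres at day 0 (an assumption; no baseline distribution is given), there is little to adjust for. For anti-spike it is plausibly larger, because all participants must have had a primary COVID-19 course and day 0 titres are likely to vary. That outcome is secondary and unpowered, and its day 28 contrast compares boosted with not yet boosted participants. The change does not repair the sample size calculation.

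**What to change.** In the SAP, before unblinding:

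1. Estimate the between-group GMT ratio at day 28, and at day 180, by ANCOVA on log10 titre with group and log10 day 0 titre of the same antigen. Back-transform the estimate and its confidence interval. Do this for anti-GP and for anti-spike.
2. Report the unadjusted log-scale GMT ratio as a sensitivity analysis.
3. State that day 0 sera are assayed alongside the later samples, and amend the assay sentence in Blood sampling to say so.

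The cost is SAP wording, about one degree of freedom per model, and the day 0 assays if they are not already planned. The article says recruitment had not opened and the SAP was still to be finalised, so the choice can be made without sight of results. Adjustment chosen after unblinding would be open to a charge of selection.
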